### Objectives {7}

This study is a non-inferiority trial that aims to compare the effect of Oral Transmucosal (OT) haloperidol and olanzapine in the management of terminal delirium in dying patients receiving home hospice care. The study’s secondary objective is to record the frequency and severity of toxicity from treatment. It is hypothesised that OT Haloperidol will reduce the severity of agitation and of terminal delirium as effectively as OT olanzapine, i.e. Haloperidol will not perform “unacceptably worse” than olanzapine.

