### Outcomes {12}

The primary outcome is the reduction in delirium severity as measured with the Memorial Delirium Assessment Scale (MDAS). Secondary outcomes are the reduction in the severity of agitation as measured with the Richmond Agitation-Sedation Scale modified for palliative care (RASS), and the frequency and severity of medication toxicities, as measured using the National Cancer Institute Common Terminology Criteria for Adverse Events (NCI-CTCAE). These data will be collected over four time-points: (i) baseline, (ii) 24 h after commencement, (iii) 48 h after commencement, and (iv) 72 h after commencement.

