#### The Richmond Agitation-Sedation Scale modified for palliative care

The RASS is a simple observational instrument assessing levels of sedation and agitation. It requires no patient input and ranges from + 4 (overly combative) to − 5 (unarousable). It is considered less time-consuming and easier to use than other similar instruments [15]. Developed for adult intensive care unit patients, the scale demonstrated strong inter-rater reliability in that setting. A modified version was designed for use in the palliative care setting, which produced acceptable psychometric properties. Hui, et al. had caregivers using the RASS to assess patients, which gave ratings similar to clinicians [16]. As part of scoring calibration with the caregivers, the attending study team members will guide the caregivers to provide the first score during the time of the first dose. Subsequently, caregivers will chart the patient’s agitation using the RASS every 6 h after the first dose. If breakthrough medication is required, the caregiver will also chart the time of administration and provide a RASS score.

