#### National Cancer Institute Common Terminology Criteria for Adverse Events [17]

Possible side effects of taking either drug include over sedation and extrapyramidal symptoms (akathisia, extrapyramidal disorder, and spasticity). To track these adverse events and their severity, the study team physician will rate observed adverse events using the scale provided by the criteria at 24 h, 48 h and 72 h.

The trial will be conducted for up to 72 h after recruitment; the trial may be stopped earlier in the event of the patient’s death or to ensure the patient’s safety and well-being. If the patient completes the trial and survives, the patient will continue to receive support from their palliative care providers. Patients who survive beyond 7 days after recruitment will be excluded from per-protocol analysis, as they no longer fit the inclusion criteria for the study, i.e. no longer imminently dying.

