## Statistical methods

### Statistical methods for primary and secondary outcomes {20a}

For the first primary outcome, changes to the severity of delirium over three 24-h periods, as measured with the MDAS, would be analysed using repeated-measures, between-factors ANOVA. If a statistically significant difference is found between medications, post hoc analysis will be conducted to analyse the change in MDAS scores at each time-point.

The second outcome, changes in the patient’s agitation, will be measured using the RASS score. Similarly, the repeated-measures, between-factors ANOVA would be used to analyse the differences in scores.

Additional outcomes of interest are possible toxicity effects due to the medication, which is measured using NCI CTCAE. For each group, the frequency of toxicities (Akathisia, Extrapyramidal disorder, and spasticity) for each group will be compared.

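### The planned toxicity comparison omits over-sedation and severity, while the RASS score, analysed as written, would count sedation below 0 as less agitation

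*Protocol article*

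**What the plan says.** All references are to the protocol article.

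**Agitation.** Outcomes {12} states: "Secondary outcomes are the reduction in the severity of agitation as measured with the Richmond Agitation-Sedation Scale modified for palliative care (RASS"). The section on the scale says "The RASS is a simple observational instrument assessing levels of sedation and agitation", and adds: "It requires no patient input and ranges from + 4 (overly combative) to − 5 (unarousable"). Caregivers rate it at the first dose, every 6 h afterwards, and when a breakthrough dose is given. Statistical methods {20a} takes the RASS score as the measure of change in agitation and says that repeated-measures, "between-factors ANOVA would be used to analyse the differences in scores". It says nothing about scores below 0, and names no separate sedation measure.

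**Toxicity.** The section on the NCI-CTCAE says: "Possible side effects of taking either drug include over sedation and extrapyramidal symptoms (akathisia, extrapyramidal disorder, and spasticity"). The study team physician grades these events at 24, 48 and 72 h. Outcomes {12} defines the toxicity outcome by both frequency and severity, with no restricted list. Statistical methods {20a} then plans the comparison between arms: "the frequency of toxicities (Akathisia, Extrapyramidal disorder, and spasticity) for each group will be compared".

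**The concern.** Two features of Statistical methods {20a} act on the same event, a patient who becomes deeply sedated.

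- The list of toxicities to be compared consists of exactly the three extrapyramidal terms from the CTCAE section. Over-sedation, which that section names first, is dropped. Only frequency is compared, so a mild and a severe event weigh the same.
- RASS puts agitation and sedation on one signed scale. When the outcome is a reduction in agitation and the score is used as it stands, a point lost below 0 counts the same as a point of agitation relieved.

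If one arm sedates more than the other, the agitation comparison could move in its favour while the named toxicity comparison shows no cost. Objectives {7} applies the hypothesis that haloperidol is not unacceptably worse to agitation as well as delirium. Extra sedation in the haloperidol arm could therefore make it look better on agitation than it is, and extra sedation in the olanzapine arm could make haloperidol look worse than it is.

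**Working it through.** The plan gives no RASS figure to reproduce. The check sets the sections side by side and then does arithmetic on assumed values.

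**Step 1: the toxicity terms.**

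| Item | CTCAE section | Outcomes {12} | Statistical methods {20a} |
|---|---|---|---|
| Over-sedation | named, graded at 24, 48, 72 h | covered (no list) | not listed |
| Akathisia, extrapyramidal disorder, spasticity | named, graded | covered | listed |
| Frequency | – | yes | yes |
| Severity | graded | yes | not compared |

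The analysis is narrower than the outcome it serves in two respects: one event and one dimension.

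**Step 2: size of the RASS effect, over-sedation only.** Inputs from the article: the scale runs from +4 to −5, and the outcome is a reduction. Assumptions, because the article gives no RASS data: 0 is the calm point between the two sides, both arms start at +2, and over-sedated patients sit at −4. In arm A everyone reaches 0. In arm B a share s goes to −4 and the rest reach 0.

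- Arm A: mean change = 0 − 2 = −2.0.
- Arm B: mean change = s × (−4) + (1 − s) × 0 − 2 = −2 − 4s.
- Apparent advantage of B = 4s, or 0.4 points for each 10% of patients.

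**Step 3: over-sedation together with poorer agitation control.** As in step 2, but the rest of arm B stay agitated at +1.

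- Untransformed: s × (−4) + (1 − s) × 1 − 2 = −1 − 5s.
- Scores below 0 set to 0: s × 0 + (1 − s) × 1 − 2 = −1 − s.

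| s | Arm A | B, rest at 0, untransformed | B, rest at +1, untransformed | B, rest at +1, scores below 0 set to 0 |
|---|---|---|---|---|
| 10% | −2.0 | −2.4 | −1.5 | −1.1 |
| 20% | −2.0 | −2.8 | −2.0 | −1.2 |
| 30% | −2.0 | −3.2 | −2.5 | −1.3 |
| 50% | −2.0 | −4.0 | −3.5 | −1.5 |

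In the first scenario B looks better by 0.4 to 2.0 points with no better control of agitation. In the second, B ties with A at s = 20%, although 80% of its patients are still agitated and the other 20% are over-sedated. Above 20% it looks better. On the agitation part alone B stays behind A throughout, and in the first scenario the two arms are equal at −2.0.

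**Step 4: limit of the simple repair.** With scores below 0 set to 0, a patient at −5 and a patient at 0 both score 0. The agitation part therefore removes the extra credit for sedation but does not show the sedation. It has to be read beside a sedation measure.

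**The case against.** The strongest reply is that over-sedation is not ignored. It is graded at every visit, it falls within the general toxicity outcome of Outcomes {12}, the Abstract says toxicities will be compared, intolerable toxicity ends a patient's participation, and related adverse events are recorded. This stands. A reader might infer that the trial never counts sedation as a harm, and the documents do not support that. What remains is that the one place that specifies the comparison gives a list without it.

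A second reply is that no section says a negative RASS score is a benefit, and that scoring rules are commonly left to an analysis plan, which is not shown. This stands in part. The credit for sedation follows only if the score is analysed untransformed, so the point is conditional. But the article does fix the score as the measure of change in agitation, and nothing in it prevents this reading.

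Three further readings are tempting and should not be made:

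- That the analysis breaks Objectives {7} by leaving out severity. That section says the "secondary objective is to record the frequency and severity of toxicity from treatment", and the grading does that. The mismatch is with Outcomes {12}.
- That one named drug is favoured. Over-sedation is listed for either drug, and no section says which sedates more. If sedation is similar in both arms, the contrast between them is little affected.
- That patients who start at or below 0 add only noise or sedation. They can become agitated during the 72 h, which is real information. A patient who moves from −3 to 0 would score as worse on the untransformed scale.

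**Conclusion.** The concern holds in a limited form. It is certain from the text that the named toxicity comparison leaves out over-sedation and severity, against the article's own side-effect list and outcome definition. It is conditional that the RASS analysis credits sedation: this follows if the signed score is used untransformed, as the wording has it, and it biases the comparison only if the arms differ in sedation.

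The size cannot be estimated from the documents. The range of 0.4 to 2.0 RASS points for 10% to 50% of patients at −4 instead of 0 is an illustration on assumed values. These are secondary outcomes, but one carries the agitation part of the hypothesis and the other the whole planned safety comparison. The change should be made, preferably before outcome data are seen, since the trial is open-label.

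**What to change.** 1. In Statistical methods {20a}, add over-sedation to the toxicities compared between arms. Compare the worst CTCAE grade per patient as well as frequency, to match Outcomes {12}.
2. Define the agitation analysis on the positive side of RASS, for example the share of a patient's ratings at +1 or above, using the 6-hourly caregiver ratings.
3. Always report beside it a separate comparison between arms of sedation depth, taken from the negative RASS values, because the agitation part alone scores an unarousable patient the same as a calm one.

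The cost is a change of wording and a little more analysis; no new data are needed. There are two small downsides. If max(RASS, 0) is used as the agitation score, many values tie at 0, which suits the planned ANOVA poorly; the share of ratings at +1 or above is easier to interpret. And sedation near death partly reflects dying itself, so its absolute level should be read with care, although randomisation should balance that part between arms.

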### Interim analyses {21b}

Not applicable.

### Methods for additional analyses (e.g. subgroup analyses) {20b}

Not applicable.

### Methods in analysis to handle protocol non-adherence and any statistical methods to handle missing data {20c}

Given the unstable state of the patient, and the community setting being a more difficult-to-control environment, protocol non-adherence may occur due to a variety of real-world factors. The investigators will document instances of non-adherence and assess if the patient would need to be withdrawn from the trial; patient safety and comfort would be prioritised.

To handle protocol non-adherence, analysis will be done on an intention-to-treat analysis basis; participants would be classified according to the treatment they were originally randomised. This analysis method would best reflect the original trial design.

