### Criteria for discontinuing or modifying allocated interventions {11b}

The study will be terminated for that patient in any one of the following situations:
Midazolam injectable rescue medication is used, or the allocated daily dosage limit is reached.Toxicities related to the trial medication were observed to be intolerable.Proxy asks to withdraw the patient from the study.Patient is admitted to the hospital.

The study may be terminated at any point during the trial. In that event, the investigators will record the reason for cessation, and make a final assessment of the patient, where applicable. The patient will continue to receive support from their palliative care providers. Data from the patient will be included for analysis up to the point of discontinuation; subsequent time points will not include that patient.

The proxy or the patient may choose to withdraw participation from the study at any time, without compromising further treatment using other drugs or alternative dosage regimen. The patient’s primary palliative nurse will be informed, and they will continue to arrange and provide medical care and hospice support for the patient, in the usual way outside of research. They will advise how persisting symptoms should be managed, outside of the study.

If voluntary withdrawal occurs, the patient will be asked to continue scheduled evaluations, complete an end of study evaluation, and be given appropriate care under medical supervision until the symptoms of any adverse event resolve or the patient’s condition becomes stable.

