### Provisions for post-trial care {30}

As this trial involves patients whose prognoses are between 3 and 7 days, patient death is expected by the end of the trial. However, in the event the patient outlives the prognoses and survives, the patient’s primary nurse and staff will continue to provide standard palliative care to the patient. At this point, medical advice and end-of-life decisions will be made independently from the study. The patient’s survival (whether alive, discharged, or deceased) will be monitored up to day 7 of recruitment. If the patient is still alive after day 7, their data will be removed from the main analysis as they would no longer fall under the inclusion criteria of an imminently dying patient.

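### In a declared non-inferiority trial, expected non-adherence is handled by intention-to-treat only, and the one per-protocol exclusion stated concerns survival, not dosing

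*Protocol article*

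**What the plan says.** All references are to the Protocol article.

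- **Objectives {7}** sets the framework: "This study is a non-inferiority trial that aims to compare the effect of Oral Transmucosal (OT) haloperidol and olanzapine". The hypothesis is that haloperidol is not unacceptably worse than olanzapine.
- **Section {20c}**, on non-adherence and missing data, expects the problem: "protocol non-adherence may occur due to a variety of real-world factors". Instances are to be documented and each patient assessed for possible withdrawal. The analytic answer is "To handle protocol non-adherence, analysis will be done on an intention-to-treat analysis basis; participants would be classified according to the treatment they were originally randomised", with the reason "This analysis method would best reflect the original trial design".
- **The NCI-CTCAE subsection of {18a}** contains the only mention of a per-protocol analysis: "Patients who survive beyond 7 days after recruitment will be excluded from per-protocol analysis".
- **Provisions for post-trial care {30}** gives the same survival rule a different target: "If the patient is still alive after day 7, their data will be removed from the main analysis".
- **Criteria for discontinuing {11b}** limits what enters any analysis: "Data from the patient will be included for analysis up to the point of discontinuation; subsequent time points will not include that patient".
- **Intervention description {11a}** has investigators review patients at home daily over the 72 h and confirm that doses used match doses documented.

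**The concern.** In a superiority trial, patients who do not take their assigned drug dilute the contrast, which works against the claim. In a non-inferiority trial the same dilution can work for the claim, because a real deficit looks smaller than it is. Saying that intention-to-treat best fits the design therefore overlooks what the stated objective requires.

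The setting makes this relevant. Family caregivers give the doses at home to unstable, dying patients, and the protocol itself foresees departures. If missed doses made the arms look alike, the trial would not have answered whether haloperidol is unacceptably worse as a drug. The survival-based exclusion cannot reveal this, since a patient who dies within 7 days may have had every dose due or almost none.

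The analysis sets also conflict. Taking day-7 survivors out of the main analysis, on an event after randomisation, is not intention-to-treat as {20c} describes it. Nor do {30} and {18a} agree on which analysis loses those patients.

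**Working it through.** **Inputs from the document (Sample size {14}, Table 3).** SD 7.64 MDAS points; minimal important difference 2 points; 32 per arm; alpha 0.05, sidedness not given; expected reduction on either drug 7–8 points.

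**Assumptions of this check.** The 2 points serve as the non-inferiority limit, although the protocol does not call them a margin. The protocol gives no non-adherence rate, so 10–30% per arm is used. Non-adherent patients show no drug difference. One comparison of means is made.

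**The plan's own figure.** The 32 per arm does not follow from a simple two-mean formula: 2 × (1.960 + 0.842)² × (7.64/2)² is about 229, or 230 per arm with rounding and normal quantiles at full precision. Table 3 names a repeated-measures design but gives no correlation. That is a separate matter, and 32 is taken here as stated.

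**Step 1: dilution with equal non-adherence p in both arms.** With a true deficit of 2 points, the observed deficit is 2(1 − p).

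**Step 2: standard error.** SE = 7.64 × √(2/32) = 7.64 × 0.25 = 1.91.

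**Step 3: chance of a false non-inferiority claim** when the true deficit equals the limit: Φ(2p/SE − z), with z = 1.960 for 2.5% and 1.645 for 5%, both one-sided.

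| p per arm | Observed deficit | 2p/SE | Nominal 2.5% becomes | Nominal 5% becomes |
|---|---|---|---|---|
| 0% | 2.0 | 0 | 2.5% | 5.0% |
| 10% | 1.8 | 0.105 | 3.2% | 6.2% |
| 20% | 1.6 | 0.209 | 4.0% | 7.6% |
| 30% | 1.4 | 0.314 | 5.0% | 9.2% |

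**Sensitivity to the SD.** The SD at which 32 per arm would give 80% power is 2 / (0.25 × 2.802) = 2.86. With that SD, the 2.5% column reads 4.7%, 8.1% and 13.1% for p = 10%, 20% and 30%.

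**Step 4: direction when the arms differ.** Take a reduction of 7.5 points on olanzapine (the middle of 7–8) and 5.5 on haloperidol, a true deficit of 2, with no reduction in undosed patients. The observed deficit is 7.5(1 − q_O) − 5.5(1 − q_H), where q_O and q_H are the undosed fractions on olanzapine and haloperidol.

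- 20% undosed in both arms: 6.0 − 4.4 = 1.6, towards non-inferiority.
- 20% undosed on olanzapine only: 6.0 − 5.5 = 0.5, strongly towards it.
- 20% undosed on haloperidol only: 7.5 − 4.4 = 3.1, against it.

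The deficit falls below 2 only when 7.5 q_O exceeds 5.5 q_H, that is, when q_H is less than about 1.36 q_O. Similar rates, or more non-adherence on olanzapine, meet that condition. Non-adherence concentrated on haloperidol does not.

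**The case against.** The strongest reply has five parts.

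1. **A per-protocol analysis is evidently planned.** The NCI-CTCAE subsection mentions one exclusion in passing and does not say it is the only one. A reader might infer that the per-protocol set is defined by survival alone. The text does not support that, and a fuller definition may sit in documents not shown. What stands is that {20c} itself names a single remedy for non-adherence and gives a reason for it that does not suit the objective.
2. **Many badly non-adherent patients leave the data.** Section {11b} stops their contribution at discontinuation. This does limit the dilution. It does not remove it, because withdrawal for non-adherence under {20c} is a judgement, so under-dosed patients can remain.
3. **Fully undosed patients should be few.** The first dose is supervised, visits are daily and a helpline is open. This stands: partial dosing would usually dilute less than the table assumes.
4. **The direction is not fixed.** A reader might infer that the plan is shown to be biased towards non-inferiority. It is not. The preparations differ (drops against a tablet), so equal adherence cannot be presumed, and Step 4 shows the reversal. However, intention-to-treat alone cannot show which pattern occurred.
5. **The error rates belong to a test the protocol does not state.** Section {20a} specifies a repeated-measures ANOVA and no comparison with a margin. This also stands, so the rates are illustrative. Dilution would equally pull an ANOVA contrast towards no difference.

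Requiring success in both analyses would be costly here. Doses taken may depend on consciousness, swallowing and prognosis, and the set would be smaller than one that is already small. That argues for a supporting role, not against the analysis.

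**Conclusion.** The point holds in a limited form. The protocol chooses intention-to-treat as its one stated answer to expected non-adherence, for a reason that overlooks the non-inferiority objective, and no stated analysis looks at patients dosed as planned. This can favour the claim. Whether it does depends on how non-adherence is spread between arms, and the protocol gives no figures on that.

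Under equal non-adherence the effect is moderate: at most a doubling of a nominal 2.5% error at 30% with the plan's SD, and more if the effective SD is smaller. These sizes rest on the assumed limit, the assumed rates and no drug difference in non-adherent patients.

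The conflict over day-7 survivors needs no assumption. Sections {18a}, {20c} and {30} cannot all apply as written.

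**What to change.** 1. In {20c}, keep intention-to-treat as randomised, and drop the sentence that presents it as the analysis best reflecting the design.
2. Add a pre-specified supporting per-protocol analysis of MDAS defined by dosing adherence. For example: assigned drug received, and at least a pre-set share of the regular doses due while the patient was alive and on study. Take adherence from the daily dose reconciliation in {11a}.
3. Report it beside intention-to-treat, and discuss any disagreement before claiming non-inferiority.
4. Make {18a}, {20c} and {30} agree on which analysis, if any, leaves out patients alive after day 7.

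**Cost.** Wording and one further analysis on data already collected, with no change to treatment or visits. The adherent set is smaller and not protected by randomisation, since doses taken may depend on prognosis, so it supports intention-to-treat and does not replace it.
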